### Statistical analysis of the 16S rRNA data and predicted microbial metabolic pathways

ASV counts will be normalized using cumulative sum scaling [68]. Differences in community richness, evenness, and structure [alpha (i.e., Shannon index) and beta diversity (i.e., Unifrac [69] and Bray-Curtis distances)] between groups will be determined using PERMANOVA from vegan R package. Generalized linear mixed models (GLMMs) will determine the phenotypic variables, cardiometabolic outcomes, and BA-associated variables associated with each microbial ASV and genus level as implemented in MasLin [70], with treatment group as the main fixed factor, adjusting for important covariates, such as age and medication usage. Multiple comparisons will be adjusted using false discovery rate (FDR) [71]. An FDR-corrected *p*-value ≤ 0.001 will be deemed significant. All analyses will be done with R using functions encoded in the phyloseq package [72]. ASVs will be employed to determine the most likely associated microbial genes that encode for enzymes and associated microbial metabolic pathways using PiCRUSt2 [45]. GLMMs will be employed to determine the genes and metabolic pathways associated with each intervention arm with MasLin [70]. Finally, we will determine the likelihood that the ensemble of microbial genes associated with the production and consumption of DCA and H_2_S are affected by the interventions.

### Statistical analysis of specific microbial target genes from qPCR and SCFAs

Microbial gene targets obtained via qPCR will be examined for distribution and transformed if appropriate to examine within and between group changes and differences at mid-study and post-intervention [7]. We will also examine associations between the microbial gene targets and serum and fecal BAs, circulating pro-inflammatory cytokines, and metabolic markers (e.g., fasting glucose) using principal component analyses, and canonical correspondence analyses as we have done previously [73]. Multiple linear regression analysis will be used to identify which determinant variable changes (e.g., fecal BAs) are independently associated with changes in microbial gene targets from baseline to mid-study and post-intervention, controlling for participant-level covariates such as age and medication usage.

### Gene expression analysis in exfoliated intestinal epithelial cells

We will test for differential gene expression (DE) in the exfoliome of participants using the generalized linear models available in edgeR, followed by FDR correction [71]. The DE genes will be interrogated by the Ingenuity Pathway Analysis (Qiagen, Hilden, Germany) software and enriched regulatory pathways will be identified as previously described [49].

### Feature selection based on linear discriminant analysis (LDA)

We will consider the regulatory genes expressed in the host exfoliome [74], the gut microbial ASVs, fecal BAs, and SCFAs as four categories of features in a classification problem that aims to detect sets of features (from the four feature categories) that best discriminate among the four groups. We will search all subsets of five or fewer features and test for significance using LDA [75, 76]. Sets with a low bolstered resubstitution misclassification error [77] (≤ 0.10) will be reported.

### Modeling of regulatory networks between the gut microbiome and human colonocytes

Our objective is to computationally model the host regulatory networks following exposure to the lifestyle interventions. Mathematical modeling of relationships in a gene regulatory network was originally proposed by Dougherty et al. [75] and further developed by members of our team [78]. We will use the concept of coefficient of determination (CoD) [79], which has previously been used to measure multivariate nonlinear gene interaction [75], and define the expectation that a master regulatory gene, when active, will be responsible for regulating one or more cascades of subsequent changes in the activity of other members of the respective pathway(s). This approach models a probabilistic relationship between regulators and regulated and derives the CoD of the master regulatory gene relative to the regulated [80]. The validation of the model for the case of gene regulatory networks has been performed as previously described [80–82] and can be readily extended to any regulatory cascade including bacterial species and microbially-produced metabolites (e.g., SCFAs, DCA) that interact with the host gut. Comparisons between the groups of participants will allow us to model the microbial consortia regulatory actions as modifiers of signaling cascades in colonocytes. Because the CoD does not imply directionality, we will incorporate existing knowledge of regulatory networks to constrain the space of possible solutions. We will also use this approach to discover novel regulatory relationships between the features used in our model.

### sCCA data integration

To assess the interdependencies among fecal microbiome, BAs, SCFAs, and host intestinal physiology in the intervention arms, we will deploy sparse Canonical Correlation Analysis (sCCA) [74, 83]. The groups of host genes, microbial ASVs, and microbial metabolites (i.e., SCFAs, DCA) identified by the 3-way sCCA will indicate potential biomarker sets for the participants in each one of the three intervention arms. We will also compare the 3-way correlative structures detected in each one of those groups to the others to elucidate the effects of the dietary interventions on the interactions between the host microbiota and the human gut relevant to CRC prevention and progression.

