### Randomization

The data manager, who has no contact with participants, will use the REDCap randomization module to randomly assign participants to (1) Med-A, (2) WL-A, (3) WL-Med, or (4) TDC, in a 1:1:1:1 allocation ratio. Stratified block randomization will be adopted to ensure good balance among the four study groups with respect to the selected covariates: sex, age (45–60 or 61–75 years), and baseline BMI (30–39.99 or 40–50 kg/m^2^). The randomization allocation will be created in SAS and imported into the REDCap randomization module.

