### Control (TDC) participants

A research team member will meet individually with the TDC participants at the start of the intervention. They will not receive information about making diet or physical activity changes and will be asked to maintain current diet and physical activity behaviors. Additionally, they will receive weekly health newsletters about non-diet related health topics (e.g., flu prevention). All WL-Med materials will be offered to the TDC participants in a self-guided format following the intervention.

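### The sCCA is described for the three intervention arms only, so it cannot say whether structures common to those arms were induced by the interventions, nor estimate any arm's effect against typical diet

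*Protocol article*

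**What the plan says.** The trial has four randomised arms. Under Randomization, the data manager will "randomly assign participants to (1) Med-A, (2) WL-A, (3) WL-Med, or (4) TDC, in a 1:1:1:1 allocation ratio". The Introduction frames the trial question as each of the first three arms against TDC, for bile acid metabolism, gut microbiota and intestinal epithelial markers. Under Control (TDC) participants, the control arm "will be asked to maintain current diet and physical activity behaviors".

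The section on sCCA data integration is narrower. Its opening sentence places the analysis in the intervention arms. The sets it finds are to serve as "potential biomarker sets for the participants in each one of the three intervention arms". The plan is then to "compare the 3-way correlative structures detected in each one of those groups to the others", and the purpose is "to elucidate the effects of the dietary interventions on the interactions between the host microbiota and the human gut". The section names neither TDC nor a comparison with baseline.

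The LDA section, which uses much the same feature types, counts the arms differently: it seeks feature sets "that best discriminate among the four groups". Table 2 schedules bile acids, short-chain fatty acids, 16S microbiota and exfoliated-cell expression at all three visits, with no restriction by arm.

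**The concern.** The stated purpose is to learn about intervention effects, but the analysis as described leaves out the only arm that received none of the interventions. Host genes, gut bacteria and their metabolites are correlated in people who change nothing. A gene–microbe–metabolite set that appears in all three active arms could therefore be ordinary biology, or it could be a response that every intervention produces. Influences shared by all participants add to this: the common ban on prebiotics, probiotics, fiber supplements and laxatives through the last visit, and recruitment in three cohorts. TDC is the concurrent group with those influences and without the lifestyle interventions.

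At stake is the reading of the arm-specific biomarker sets. They could be reported as products of an intervention without any check that they differ from what is seen under typical diet.

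**Working it through.** **The plan's figure for arm size.** The Sample size section gives 41 completers per group (effect size 0.67, one-sided level 0.05/3, power 0.80). This reproduces: with the noncentral t distribution, power is 0.806 at 41 per group and 0.795 at 40. With 15% dropout, 48 × 0.85 = 40.8, or about 41 per arm. The figure was set for the bile acid tests. It is used here only to say how many TDC participants could supply a reference.

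**Counting comparisons.**
- Three intervention arms: 3 × 2 / 2 = 3 pairwise comparisons, 0 of them with TDC.
- Four arms: 4 × 3 / 2 = 6 pairwise comparisons, 3 of them with TDC.

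**What the three active comparisons can show.** From the calorie and nutrient recommendations (Table 1) and the Food delivery and Physical activity sections:
- WL-Med versus WL-A: both have the calorie deficit and the step goal. They differ mainly in the Mediterranean diet package. This is a randomised contrast for that package in people losing weight.
- WL-Med versus Med-A: both have the Mediterranean diet package. They differ in the calorie deficit and the step goal. This is a randomised contrast for weight loss in people on that diet.
- Med-A versus WL-A: one package against the other.

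**What they cannot show.** Write the strength of a given structure in arm k as S_k = B + D_k, where B is its value under typical diet and D_k is the change due to that arm's intervention. Then:
- Between active arms: S_j − S_k = D_j − D_k. B cancels, and so does any part of D that the arms share.
- Against control: S_k − S_TDC = D_k.

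Take B = b with every D_k = 0 (ordinary biology), and B = 0 with every D_k = b (induced by all three). Both give S_k = b in each active arm. The active arms alone cannot separate these two cases, at any sample size. For the same reason they cannot give the effect of diet alone or weight loss alone against neither, or show whether the two effects add.

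**Illustration with assumed values.** One correlation of 0.5 in each active arm, 41 per arm, Fisher z comparisons, two-sided, Bonferroni over three, 4,000 simulated runs. The figures are the share of runs in which at least one of the three comparisons is flagged.

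| Truth in TDC | Among active arms | Active versus TDC |
|---|---|---|
| Correlation also 0.5 (no effect) | 4.4% | 4.5% |
| Correlation 0 (induced by all three) | 4.4% | 77% |

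Hand check on the last cell: atanh(0.5) = 0.549; the standard error of a difference is √(2/38) = 0.229; the ratio is 2.39, against a critical value of 2.39. Each single comparison with TDC is therefore flagged about half the time, which is compatible with 77% for at least one of three.

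The equal figures in the middle column follow from the set-up, because the active arms are identical in both rows. The simulation concerns a single correlation. It makes the algebra concrete and says nothing about the power of sCCA with many features.

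**The case against.** The strongest objection is that the active arms are themselves randomised and overlap by design. A structure present in WL-Med and absent in WL-A has a randomised comparator, and the Discussion makes separating weight loss from dietary change an explicit aim. This stands in full. A reader might infer that without TDC no detected structure can be attributed to any intervention. The documents do not support that. The gap covers only structures shared by the arms and effects against no intervention.

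Second, the section is a short summary in an article, the full protocol is not shown, and the wording about comparing structures to the others could be stretched to include TDC. The more natural antecedent is the three arms just counted, and the LDA section says four where four are meant. Counting the arms is a stated choice, not an omitted detail. Still, if TDC was intended, one sentence would settle the matter.

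Third, the analysis is exploratory and yields only potential biomarker sets, while the LDA covers all four groups. The first part stands and limits the weight of the point. The second does not fill the gap: LDA looks for features that classify participants by arm, not for differences between arms in how the data types correlate.

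Fourth, it might be assumed that TDC has complete data. The documents show only that the measurements are scheduled. The number of usable exfoliome, 16S and metabolite samples per arm is not given.

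**Conclusion.** The point holds within limits. As described, the sCCA supports statements about differences between active arms. It does not support statements about structures common to those arms, or about any arm against typical diet, and its stated purpose reaches further than that. None of its three pairwise comparisons involves the control.

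This rests on reading the compared groups as the three intervention arms, and on TDC being sampled as Table 2 schedules. The figure of about 41 TDC completers also assumes the plan's 15% dropout. The matter should be settled before the analysis is run. A reader should not infer damage to the trial's main conclusions: the primary bile acid outcomes do not depend on the sCCA.

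**What to change.** State that the sCCA will also be fitted in TDC, and add each active-versus-TDC comparison of structure: Med-A, WL-A and WL-Med, each against TDC. Whether a difference exceeds chance could be judged, for example, by permuting arm labels. Keep the active-versus-active comparisons as they are, with no lower standing, because they serve the aim of separating diet from weight loss.

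If TDC is deliberately left out, say so and limit the conclusion to differences between active arms.

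The first option needs no extra recruitment and no new measurements beyond those already scheduled. It costs computing time and raises the number of pairwise comparisons from three to six in an exploratory analysis. The second costs one sentence and a narrower claim.

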## Oversight and monitoring

### Organizational structure and responsibilities

This study will be conducted with a pre-specified organization structure assuming various responsibilities. Table 3 below details staff roles and duties.

**Table 3 Tab3:** Organizational roles and responsibilities

Role	Responsibilities
Principal Investigators	- Oversee all research-related activity and personnel - Publish results in a timely manner
Data and Safety Monitoring Committee (DSMC)	-Review the study protocol for any major concerns prior to implementation -Regularly review and evaluate the accumulated study data for participant safety, study conduct, and progress -Make recommendations concerning the continuation, modification, or termination of the trial
Data Manager	-Organizes electronic data -Data verification -Assist with data safety
Project Director	-Manages recruitment and data collection -Manages budget and staff -Trains and certifies staff -Interfaces with IRB to maintain ethical standards

### Data and safety monitoring

The following information will be included in the yearly reports to the Chair of our data and safety monitoring committee: study event updates (e.g., changes in personnel, recruitment strategies, testing procedures), study enrollment (actual vs. expected), baseline data on participants, recruitment and retention flow diagram, participant retention data (loss to follow up, withdrawals), and adverse health event monitoring. An adverse health event is any untoward medical occurrence experienced by a participant during participation in the clinical study. These events can be non-serious or serious. A serious adverse event is any adverse event that results in one or more of the following outcomes:A life-threatening eventInpatient hospitalization or prolongation of existing hospitalizationA persistent or significant disability/incapacityAn important medical event based upon appropriate medical judgmentDeath

### Data and safety monitoring committee

The DSMC will consist of 12 independent experts reflecting the disciplines and medical specialties (e.g., clinical trials, biostatistics, nutrition, clinical medicine) necessary to interpret data from the clinical trial and to fully evaluate participant safety. They are independent of the study sponsor and have no competing interests. The primary responsibilities of the DSMC are outlined in Table 3. The PIs will meet with the DSMC annually and will present a written and verbal report. Additional meetings will be scheduled if warranted by the data or adverse events.

### Adverse event monitoring and reporting

The DSMC Chair will be notified of all study-related serious adverse events within 48 h of discovery. The Chair will decide if further action beyond what the research team has proposed is warranted. Additionally, participants will be asked to report each adverse health event in person at study visits or during the intervention sessions, or via telephone/email/text message. The principal investigators will consult and determine the severity and appropriate response or action to the reported adverse health event. All serious unanticipated problems or serious adverse health events will be reported to the UIC Institutional Review Board and Office for the Protection of Research Subjects.

UIC Office for the Protection of Research Subjects requires that all other problems (non-serious adverse events) be reported within 5 days of discovery and provide sufficient information to gauge severity and to complete reports. UIC Office for the Protection of Research Subjects has procedures in place to review the reports, and the PIs are notified if further review, changes to research protocol or consent form, or other action is required. The PIs will notify NIH should UIC IRB require further action after any unanticipated problem/adverse event is reported.

UIC has not set aside money to pay participants if they get ill or injured from being in the study. The only exception to this policy is if it is proven that a participant’s injury or illness is directly caused by the negligence of UIC.

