### Individual sessions

Participants in Med-A, WL-A, and WL-Med will meet with their interventionist once weekly in-person or via Zoom (based on participant preference) for 24 sessions. Two of these sessions will be “floating” to allow for holidays that may interfere with the once-weekly plan. Weekly session content is manualized and includes time to address successes and barriers and problem solving using motivational interviewing techniques. Week one is planned as a 1-h session, with the remaining 23 weeks planned as 30-min sessions. For participants randomized to Med-A and WL-Med, the interventionist will instruct on and support the adoption of an eating pattern consistent with a MedDiet using an individualized MedDiet exchange list and companion guide [29, 30]. The exchange list will contain several categories of foods and beverages characteristic of a MedDiet (e.g., low-fat dairy). Participants will be advised to consume a specific quantity of food and beverage from each category, but will be free to choose which foods and beverages from each category they would like to consume.

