## Study outcomes and data collection procedures

### Outcomes

The primary study outcomes are total circulating and fecal BAs, taurine-conjugated BAs, and DCA. Secondary outcomes include body weight, body composition, dietary change (i.e., MedDiet adherence), physical activity (i.e., steps per day), metabolic risk, circulating cytokines (e.g., IL-6, TNFα), gut microbial community structure and composition, fecal short chain fatty acids (SCFAs) (i.e., butyrate, acetate, propionate), and exfoliated intestinal cell gene expression levels. Data collection will take place at UIC and by telephone at baseline, month 3, and study end. All data collection staff will be trained and certified in informed consent, testing procedures, specimen processing, and data management. All procedures will be written and stored electronically. Major changes to study design will first be reviewed and approved by the IRB before implementation. The primary data collectors and lab technicians will be blinded to randomization group assignment by having the assignment hidden from view in their individual REDCap account.

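### Adverse events can be reported at weekly sessions that only the three active arms have, so any by-arm table of non-serious events is open to ascertainment bias

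*Protocol article*

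**What the plan says.** In the protocol article, the section Adverse event monitoring and reporting states that "participants will be asked to report each adverse health event in person at study visits or during the intervention sessions", and then adds "or via telephone/email/text message". The added routes are not limited to any arm, and no schedule is attached to them.

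The section Individual sessions limits the sessions to three arms: "Participants in Med-A, WL-A, and WL-Med will meet with their interventionist once weekly in-person or via Zoom". It also gives their number: "Week one is planned as a 1-h session, with the remaining 23 weeks planned as 30-min sessions".

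For the control arm, the section Control (TDC) participants says: "A research team member will meet individually with the TDC participants at the start of the intervention". After that, "they will receive weekly health newsletters about non-diet related health topics". No query about adverse events is described with the newsletter.

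The visits are common to all arms. The section Outcomes says: "Data collection will take place at UIC and by telephone at baseline, month 3, and study end". It also states that the primary data collectors are blinded to assignment.

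**The concern.** Put together, these sections tie part of adverse-event reporting to a contact schedule that belongs to the intervention. A mild event in an active participant meets a scheduled staff contact within about a week. The same event in a control participant either waits for the month 3 or study-end visit or has to be reported by telephone, email or text without a scheduled prompt.

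The article defines an adverse event broadly, covering non-serious as well as serious occurrences, so many events will be of the kind that is forgotten or judged not worth a call. If the arms are later compared on such events, an excess in the active arms could reflect more frequent contact alone. A true excess could equally be dismissed on that ground.

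The extra reporting stream also differs in who receives it. According to Intervention instructors, each arm has its own interventionist, who therefore knows the assignment, whereas the visits are staffed by blinded primary data collectors.

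**Working it through.** The plan gives no figure on this point to reproduce. The check has two parts.

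**Scheduled occasions after randomisation**
- Active arms: 1 + 23 = 24 sessions (Individual sessions), plus 2 post-baseline visits (Outcomes) = 26.
- TDC: 1 start meeting (Control (TDC) participants), plus the same 2 visits = 3.
- Ratio 26/3 ≈ 8.7; difference 26 − 3 = 23.

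The start meeting comes before follow-up events can accrue. If it is dropped, the active arms' first session should be dropped as well, which gives 25 against 2, ratio 12.5, and again a difference of 23. Setting 26 against 2 (13-fold) would count the first contact in one arm and not in the other.

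Over 6 months, taken as 26 weeks, the gap between occasions is about 1 week in the active arms and 26/2 = 13 weeks in TDC.

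**Illustration of what this could do**

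The document gives no recall or volunteering rates, so the following values are assumptions. True event rates are equal in all arms. Events fall uniformly between occasions, every scheduled session is attended and serves as a reporting occasion, recall decays exponentially with half-life h weeks, and a share u of events is volunteered in every arm whatever the schedule.

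- k = ln 2 / h
- Mean recall over a gap of T weeks: f(T) = (1 − e^(−kT)) / (kT)
- Captured share: active = u + (1 − u)·f(1); TDC = u + (1 − u)·f(13)

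Example with h = 4 and u = 0.25: f(1) = 0.918 and f(13) = 0.397. Active = 0.25 + 0.75 × 0.918 = 0.939; TDC = 0.25 + 0.75 × 0.397 = 0.548; ratio 1.71.

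Ratio of captured events, active to TDC:

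| h (weeks) | u = 0 | u = 0.25 | u = 0.50 | u = 1 |
|---|---|---|---|---|
| 2 | 3.85 | 2.13 | 1.51 | 1.00 |
| 4 | 2.31 | 1.71 | 1.37 | 1.00 |
| 8 | 1.60 | 1.38 | 1.22 | 1.00 |
| 26 | 1.17 | 1.12 | 1.08 | 1.00 |

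Under these assumptions the ratio never falls below 1. Its size runs from nothing to nearly fourfold, so the table shows sensitivity and is not an estimate.

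**The case against.** The case on the other side is substantial.

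- **No between-arm safety comparison is planned in the article.** A reader might infer that the Data and Safety Monitoring Committee (DSMC) is shown a biased comparison. The Oversight and monitoring sections describe safety review and the contents of a yearly report, but no by-arm table. Safety is not a listed outcome, and no adverse-event analysis is described. This stands: the point concerns any by-arm table that may be made, not one the article commits to.
- **Sessions are named as an occasion to report, not as a scripted enquiry.** The described session content contains no adverse-event question. This stands too: 24 sessions are 24 opportunities, and treating them as 24 active enquiries is inference.
- **Control participants are also asked to report and have remote routes.** True. Those routes are open to every arm, however, and have no schedule, so they do not replace a weekly meeting.
- **The control arm still yields a background rate.** A reader might infer that it gives none. The shared visits with blinded primary data collectors contradict that. Health history including bowel health (baseline and month 6) and medication use (all three time points) are also collected in all arms.
- **Serious events are less exposed.** They are harder to forget, and study-related ones go to the DSMC Chair within 48 hours of discovery in any arm. This largely stands, although the clock starts at discovery, which can come later in TDC.
- **The article is a condensation.** Question wording, a source field and table layouts may be in the full protocol, and their absence here is no fault. The unequal occasions, by contrast, follow from rules that the article does state.

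**Conclusion.** The point holds in limited form. Followed as written, the plan gives active participants about 26 scheduled reporting occasions after randomisation and control participants 3. Any by-arm tabulation of adverse events, mainly non-serious ones, is therefore open to bias towards more recorded events in the active arms.

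The direction rests on two assumptions: that some events are forgotten or not volunteered between contacts, and that sessions are in fact used to report them. The size depends on recall and volunteering rates that the document does not give. It would be wrong to read the text as establishing that control events are under-recorded by a known amount.

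The primary and secondary outcomes are not affected. This is a worthwhile low-cost improvement, not a flaw that threatens the trial's main conclusions.

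**What to change.** - At the month 3 and month 6 visits, ask one standard adverse-event question in all four arms, covering the period since the last visit.
- Record the source of each report: visit, session or volunteered.
- Base any by-arm table, for the DSMC or for publication, on visit-elicited events plus all serious events. List session-only events separately, so that nothing is lost for safety oversight.

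The article already names study visits as a reporting occasion. The change therefore adds a scripted question, one form field and a tabulation rule, and needs no new contact. The downside is that mild events in the comparable set are recalled over about 12 weeks (half of the 24-week programme), so some will be missed, but by the same method in every arm.
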